#### Residual Tobacco Toxin

Surface dust sampling was collected from two locations—the home and the dashboard of the car—to assess for the presence of THS or residual nicotine and NNK remaining on surfaces after the cigarette was extinguished. A presoaked all-natural cotton wipe was used for surface dust collection. The cotton wipe was soaked with a solution consisting of 1.5 mL of 1% ascorbic acid mixed in reagent-grade water for sample preservation [44]. A 10 × 10 cm wire frame was created for precise marking of the sampling area. The moistened cotton wipe was swabbed over the 100-cm^2^ area on a porous location with visible dust. This sample was taken from the same room that the nicotine dosimeter was placed in as well as another central location in the home.

### Intervention Components

Participants assigned to both the active and control conditions were offered four health education brochures at the baseline assessment. Participants were provided brochures detailing information about SHS, THS (residual smoke exposure), strategies for managing parenting stress, and tips to assist in a quitting smoking attempt.

#### Biomarker Feedback Condition

In addition to the brochures detailed above, participants randomized to the biomarker feedback (active) condition were provided with baseline results from the child’s nicotine, cotinine, and NNAL urine analysis and nicotine levels found in the home and car from the nicotine dosimeter. The information was detailed in a Participant Home Report, and information was verbally reviewed by the counselor. The target behavior in counseling, determined by the participant, was either smoking cessation or the institution of complete home smoking restrictions. Counseling was administered using MAPS counseling techniques [30]. MAPS is a unique approach, derived from a motivational interviewing framework, which utilizes motivationally based techniques to enhance commitment and intrinsic motivation for change in combination with cognitive-behavioral techniques to target self-efficacy, coping, stress, and negative effects. Participants, in collaboration with their counselor, developed a wellness plan that addresses not only smoking cessation or eliminating home smoking, but also other concerns and barriers to changing their smoking behaviors, such as parenting or relationship stress.

#### Counselor Training

All counseling was delivered by a female study counselor who acted as the sole counselor for all participants randomized to the active condition. The study counselor received approximately 40 hours of face-to-face MAPS counseling training, followed by additional training until performance criteria for competence and adherence to the assigned protocol were reached. The counselor participated in monthly, individual supervision to maintain performance standards. In order to monitor protocol fidelity, all counseling sessions were audiotaped, a random sample of two of the counselor’s monthly sessions were coded, and detailed feedback was provided using a modified version of the Motivational Interviewing Treatment Integrity (3.1.1) [45] coding and feedback system to ensure adequate competence and adherence to the protocol.

The counselor followed a strict protocol for completion of the counseling visits and to maximize session adherence/retention. All five sessions were conducted within a 12-week window. The first, second, and fifth sessions were conducted in the participants home, and the third and fourth sessions were conducted over the telephone. The window allowed for sessions to be scheduled every other week until the end of the counseling window. Visits were scheduled at times negotiated between the participant and the counselor. The counselor made daily attempts to reach participants to schedule or reschedule a visit. In addition, contact letters were mailed to the participant’s current address and attempts were made to reach alternate contacts of persons listed by the participant, who would always know how to contact the participant.

#### Health Education Condition

Participants in the comparison condition received health education, which included a review of the aforementioned four health education brochures at the baseline assessment. Participants randomized to the control condition also received the baseline biomarker feedback information but at the completion of their last follow up session, to avoid influencing the study outcomes, but as a gesture of good will and gratitude for participation.

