### Outcome Assessment Visits

Assessment visits at baseline, week 16, and week 26 were scheduled at the convenience of the participant and were conducted by community health workers at the participant’s home. Visits lasted between 60 and 90 minutes. Staff administered all surveys aloud in an interview format.

Study data were collected via an iPad using a secure, Web-based data collection instrument (REDCap) [43]. At the baseline visit, staff reviewed health education brochures with each participant in a one-time education session. The brochures provided information to participants about the risks of exposure to both SHS and THS, strategies for managing parenting stress, and tips to assist in quitting smoking. A number of additional activities took place at each assessment visit and are detailed below.

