#### Nicotine Dosimeter

At each assessment visit, staff hung a passive air nicotine dosimeter [31], which is an objective, validated method to quantify the level of ambient nicotine present in the air. The dosimeters consist of a filter treated with sodium bisulfate and contained in a 4-cm polystyrene cassette. Nicotine passively diffuses to the dosimeter and binds to the filter. The nicotine dosimeter was hung in the main activity room of each home, as well as the family car, if available. The dosimeter remained in the home and car for a minimum of 7 days for sample collection. After 7 days, staff collected and shipped the dosimeter to the University of California, Berkeley, for analysis using gas chromatography to quantify the presence of nicotine in the air.

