#### Participant Incentives

At each of the three assessment visits, participants were given a choice of receiving a gift card to either a local grocery chain or a discount department store. At baseline, participants received a US $50 gift card and an additional US $5 gift card as compensation for any cell phone usage incurred from study-based calls. Participants were also provided a small gift bag including a manicure kit, a small hair towel, a bath pillow, and a body sponge. Children were given a stuffed bear named Crystal, which was designed and marked by the American Lung Association. The bear included a short poem inscribed on the tag, which read, “Second hand smoke is not a joke! Please keep clear of smoking my dear.” After completing the 16-week home visit, participants received a US $25 gift card, and a US $50 gift card was offered for completion of the 26-week visit.

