### Outcomes

#### Primary and Secondary Outcomes

The primary outcome for this study is change in home SHS exposure measured by the passive air nicotine dosimeter at 26 weeks poststudy enrollment. The specificity of the nicotine dosimeter as a marker of SHS is an appropriate marker to measure a reduction in home air nicotine. Reduction in child’s cotinine and NNAL levels and parental report of smoking behavior change (ie, cessation, quit attempts, reduction, and restrictions) served as secondary outcomes. Specifically, carbon monoxide–verified, 7-day, self-reported point-prevalence abstinence assessed 6 months after study enrollment and defined as no smoking, not even a puff, for 7 consecutive days prior to the final assessment point at month 6 served as the smoking cessation measure [47]. Using a conservative approach, participants who dropped out or were lost to follow-up were considered to be smoking. Adoption of home smoking restrictions was assessed by a question modified from the Current Population Survey Tobacco Use Supplement [48]: “Which statement best describes the rules about smoking in your home?” Participants reported whether there were no bans (“Smoking is permitted anywhere”), some restriction (”Smoking is allowed in some places or at some times”), or complete restriction or ban (“No one is allowed to smoke anywhere”). Smokers were also asked to report the number of cigarettes smoked per day and the number of quit attempts in at least 24 hours since enrollment and their use of programs (eg, Helpline) or pharmacological therapy (eg, nicotine replacement therapy and other cessation medications) at weeks 8 and 26.

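### On a plain reading, controls get their child's results as the week-26 dosimeter starts sampling, so the primary measurement may follow the feedback it was meant to precede

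*Protocol article*

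**What the plan says.** Four parts of the protocol article bear on the order of events.

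- **Outcome Assessment Visits:** "Assessment visits at baseline, week 16, and week 26 were scheduled at the convenience of the participant". Week 26 is therefore the last assessment visit. Participant Incentives agrees: "At each of the three assessment visits, participants were given a choice of receiving a gift card".
- **Nicotine Dosimeter:** "At each assessment visit, staff hung a passive air nicotine dosimeter". Then: "The dosimeter remained in the home and car for a minimum of 7 days for sample collection". Retrieval is a separate, later step: "After 7 days, staff collected and shipped the dosimeter".
- **Health Education Condition:** controls "received the baseline biomarker feedback information but at the completion of their last follow up session, to avoid influencing the study outcomes".
- **Primary and Secondary Outcomes:** the primary outcome is "change in home SHS exposure measured by the passive air nicotine dosimeter at 26 weeks poststudy enrollment". Study Design also names dosimeter air nicotine at 6 months. The Abstract instead names a home smoking restriction verified by dosimeter. Every version depends on the week-26 dosimeter.

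**The concern.** Feedback to controls was held back so that it could not affect the outcomes. That works for anything measured during the last visit. It does not work for a measurement that begins at that visit and runs for the following week, and the primary outcome is of that kind.

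The exposure would be one-sided. The active arm received its results early, as part of the intervention, so only controls would learn something new just before the decisive week. The trial's hypothesis is that learning a child's tobacco toxin levels motivates parents to restrict smoking at home. If that is right to any degree, control-arm air nicotine would fall during the sampling week and the contrast between arms would shrink. A null or weak primary result could then be read as lack of efficacy when part of it came from the order of procedures.

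**Working it through.** **Step 1: timeline on the plain reading**

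| Time | Event | Source |
|---|---|---|
| Week-26 visit | Survey, child urine and surface wipes collected; dosimeter hung | Outcome Assessment Visits and its subsections |
| End of that visit | Controls given baseline results | Health Education Condition, if the last session is the week-26 visit |
| Next 7 days or more | Dosimeter samples the air | Nicotine Dosimeter |
| After 7 days | Staff collect the dosimeter | Nicotine Dosimeter |

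Essentially all of the control arm's week-26 sampling falls after the feedback. Urine, wipes and self-report are gathered at the visit and so precede feedback given at its end. Only the week-26 dosimeter readings (home, and car where hung) are exposed. Nothing in the article says that feedback waited for retrieval, and the pick-up is nowhere called a session.

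**Step 2: reproduce the planned sample size**

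Inputs from Sample Size and Power Considerations: means 1.15 (SD 1.58) and 1.89 (SD 1.68) μg/m3, two-sided t test, type I error 0.05, 90 per group, 85% power.

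- Difference: 1.89 − 1.15 = 0.74.
- Common SD: √[(1.58² + 1.68²)/2] = √2.6594 = 1.631.
- Sample size: n = 2(1.960 + 1.036)² × 2.6594 / 0.74² ≈ 87.2, so 88 per group. The plan's 90 is consistent.
- Power at 90 per group: standard error 1.631 × √(2/90) = 0.243; noncentrality 0.74/0.243 = 3.04; power 85.7% (noncentral t) or 86.1% (normal).

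The planned figure reproduces and is not in question.

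**Step 3: what the plan implies for homes with and without a ban**

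The same section derives the means from assumed ban adoption of 55% and 25%. Let a be the mean in ban homes and b the mean in other homes.

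- 0.55a + 0.45b = 1.15
- 0.25a + 0.75b = 1.89

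Subtracting the first from the second gives 0.30(b − a) = 0.74, so b − a = 2.467. Hence b = 1.15 + 0.55 × 2.467 = 2.507 and a = 0.04. Each additional percentage point of control homes that behaves like a ban home during the week lowers the control mean by about 0.0247 μg/m3.

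**Step 4: illustration**

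The shift x is an assumption, because the document gives no effect for late feedback. Control mean = (0.25 + x)(0.04) + (0.75 − x)(2.507). The SD is held at 1.631, with 90 per arm and power from the noncentral t.

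| Assumed shift in control homes | Control mean | Difference from 1.15 | Power |
|---|---|---|---|
| 0 points | 1.89 | 0.74 | 86% |
| 5 points | 1.77 | 0.62 | 71% |
| 10 points | 1.64 | 0.49 | 52% |

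The normal approximation gives 86%, 72% and 53%. The model treats each switching home as going from 2.51 to 0.04 for the whole window, so it is a generous reading of what a given shift would do.

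**The case against.** The strongest reply is that the timing is inferred. The article never defines the last follow-up session, and it does not use the term assessment visit at that point. An assessment could involve more than one contact: at baseline there were repeat urine collections and a dosimeter retrieval, and randomization was requested from the participant's home only after final eligibility, which needed the dosimeter value. Completion of the last session could therefore mean the week-26 pick-up, and that would fit the stated purpose. This stands as an ambiguity. It does not settle the matter, because the article lists three assessment visits and does not count the pick-up among them.

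A second reply is that the exposure is weak. Controls receive only baseline results, about six months old, without the five counselling sessions or the offered nicotine replacement. The Introduction reports null findings for feedback by mailed brochure or brief phone call. The Discussion describes other smokers in the home and unsafe surroundings as obstacles to restrictions. A 10-point shift would be a third of the 30 points planned for the full package (55% − 25%). All of this stands, and it is why zero belongs in the range.

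A third reply is that enrollment and analyses are complete, so the procedure cannot be changed. That also stands. Interpretation was still under way, however, so the order of events can still be stated.

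A reader might also infer a parallel flaw at baseline, where the brochures are reviewed at the visit at which the first dosimeter is hung ("At the baseline visit, staff reviewed health education brochures with each participant in a one-time education session"). The document does not support that as a bias: every participant had the review, before randomization, so it does not favour either arm.

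**Conclusion.** The point holds as a conflict on the plain reading. The visit schedule, the dosimeter procedure and the control-arm feedback rule together put the feedback ahead of the control arm's week-26 sampling window, contrary to the reason given for delaying it. The conclusion rests on one assumption: that the last follow-up session is the week-26 assessment visit. If it is the dosimeter pick-up, the point falls away.

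Any bias would run toward no difference and would touch only the week-26 dosimeter measures, so it is not a route to a falsely positive primary result. Its size cannot be derived from the document. It may be zero or small; the 5- and 10-point rows show only how sensitive the planned contrast would be.

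A reader might infer that the primary endpoint was in fact contaminated, or that the trial's power was really 71% or 52%. Neither is supported: the first needs the actual order of events, which the article does not give, and the second needs an effect of late feedback for which the article has no figure.

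**What to change.** Reconcile Nicotine Dosimeter with Health Education Condition. Define the last session and state that controls receive their results only after the week-26 dosimeter has been retrieved, at the collection contact that staff already make after 7 days. As a procedure this adds no visit; in the article it is one sentence.

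The trial is finished, so that sentence must report what was actually done. If feedback was given at the week-26 visit, before retrieval, the authors should:

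- disclose a possible one-sided bias toward no difference in the week-26 dosimeter results;
- present the week-16 dosimeter comparison as the supporting analysis free of this problem. Those data are already collected, and Secondary Analyses already plans estimates for both arms at all three time points. Week 16 is an earlier time point, so it supports the week-26 comparison and does not replace it.

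The cost is a clarification or a short limitation statement, with no new data.

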#### Participant Incentives

At each of the three assessment visits, participants were given a choice of receiving a gift card to either a local grocery chain or a discount department store. At baseline, participants received a US $50 gift card and an additional US $5 gift card as compensation for any cell phone usage incurred from study-based calls. Participants were also provided a small gift bag including a manicure kit, a small hair towel, a bath pillow, and a body sponge. Children were given a stuffed bear named Crystal, which was designed and marked by the American Lung Association. The bear included a short poem inscribed on the tag, which read, “Second hand smoke is not a joke! Please keep clear of smoking my dear.” After completing the 16-week home visit, participants received a US $25 gift card, and a US $50 gift card was offered for completion of the 26-week visit.

### Retention

To maximize retention efforts, reminder postcards were mailed to participants a week prior to all visits, and reminder phone calls were made a day before and the day of the scheduled visit. If a visit window was missed throughout study participation, the visit was marked as missed and participant contact was initiated for the next assessment visit. To minimize attrition, staff made periodic reminder calls to participants to reschedule missed visits until the window for completing appointments closed. Participants were asked to provide their home address, home and cell phone numbers, and two alternate numbers to use in the situation that they could not be reached. Participants were also sent a holiday greeting card, child and mother birthday cards, and a thank you card during their six-month participation window.

### Data Management

All data management for this project utilized REDCap [46], a secure Web app for building and managing online surveys and databases. REDCap was used for data entry, data cleaning, identifying any crossovers, and conversion into proper format for data analysis and recoding using SAS [computer program] (Cary, NC: SAS Institute Inc). REDCap was also used to design and administer all assessment surveys. A REDCap tracking feature was also used to follow-up each patient and to prompt staff regarding upcoming data collection points.

### Outcomes

#### Primary and Secondary Outcomes

The primary outcome for this study is change in home SHS exposure measured by the passive air nicotine dosimeter at 26 weeks poststudy enrollment. The specificity of the nicotine dosimeter as a marker of SHS is an appropriate marker to measure a reduction in home air nicotine. Reduction in child’s cotinine and NNAL levels and parental report of smoking behavior change (ie, cessation, quit attempts, reduction, and restrictions) served as secondary outcomes. Specifically, carbon monoxide–verified, 7-day, self-reported point-prevalence abstinence assessed 6 months after study enrollment and defined as no smoking, not even a puff, for 7 consecutive days prior to the final assessment point at month 6 served as the smoking cessation measure [47]. Using a conservative approach, participants who dropped out or were lost to follow-up were considered to be smoking. Adoption of home smoking restrictions was assessed by a question modified from the Current Population Survey Tobacco Use Supplement [48]: “Which statement best describes the rules about smoking in your home?” Participants reported whether there were no bans (“Smoking is permitted anywhere”), some restriction (”Smoking is allowed in some places or at some times”), or complete restriction or ban (“No one is allowed to smoke anywhere”). Smokers were also asked to report the number of cigarettes smoked per day and the number of quit attempts in at least 24 hours since enrollment and their use of programs (eg, Helpline) or pharmacological therapy (eg, nicotine replacement therapy and other cessation medications) at weeks 8 and 26.

#### Treatment Effect Moderators/Mediators

In order to examine psychological mediators and moderators of the proposed intervention (exploratory aims), key factors related to important determinants of smoking behavior change were selected for each set of analyses. These included proposed moderators of effect including sociodemographic variables for parent and child, baseline smoking, and social environmental variables. Participants were asked to detail the number of days they smoked in the last 30 days, the number of cigarettes they smoked on days they smoked, use of smokeless tobacco products and other tobacco used in the last 30 days, whether they used mentholated cigarettes, the number of 24-hour quit attempts they made in the past year, the longest time period they had without smoking a cigarette, and their lifetime nicotine replacement therapy use. Other tobacco-related variables included nicotine dependence, measured using “time to first cigarette” [49] and readiness to quit smoking [50]. Alcohol use [51] (ie, number of days one drank at least one drink, number of days one drank five or more drinks) was also assessed. Social environmental variables included the number of smokers living in the home, number of adult nonsmokers living in the home, outdoor smoking options, location where most smoking occurs, and adoption of home smoking restrictions in the home and car. Child exposure to tobacco smoke was also measured (ie, exposure to tobacco smoke in the home and outside the home in the past week). To assess any potential illnesses or health conditions that might impact the intervention or its effectiveness, parents were asked the following: “Has any health care provider ever told you that your child has any of the following illnesses: (eg, asthma, allergies, cancer, heart problems)?” Psychosocial variables included depressive symptoms (assessed using the 10-item Center for Epidemiological Studies Depression Scale [52]) and stress (measured using the 4-item Perceived Stress Scale [53]). Social influence was measured by asking how many of the participant’s five closest friends smoked cigarettes [54], and social support was measured via the Partner Interaction Questionnaire (Short-Form) [55]. Participants’ view of their social standing in the community and the nation was assessed using the MacArthur Scale of Subjective Social Status [56].

Key mediators are important behaviors, attitudes, and beliefs related to both the proposed intervention and the outcomes. Optimism bias was assessed using a modified version of the Smoking Hazards Scale [57], a 12-item questionnaire with four scales designed to assess perceptions of obvious and subtle health risks due to smoking and other health behaviors. We modified the existing measure to assess perceptions regarding the child’s exposure to SHS. The Passive Smoking Outcomes Expectations Scale [17] was used to assess parents’ expectations of the outcomes that may result from their children’s exposure to SHS. Intrinsic motivation was assessed with the Treatment Self-Regulation Questionnaire [58-60]. We used this tool to measure intrinsic and extrinsic motivation in order to adopt home smoking bans and quit smoking. Smoking abstinence self-efficacy was assessed using the 12-item Smoking Self-Efficacy Questionnaire, and self-efficacy to engage in behaviors to decrease child SHS exposure (eg, adopt home smoking bans) was measured using the Passive Smoking Outcomes Expectations scale [17]. To assess whether receipt of biomarker feedback was associated with changes in motivation and confidence to quit smoking/adopt home smoking bans, participants were asked “How motivated are you to quit smoking/adopt bans?” and “How confident are you in your ability to quit smoking/adopt bans?” In order to assess message salience and comprehension, at the conclusion of each of the three counseling sessions, participants were asked a series of five questions to assess their comprehension and ability to relate to the material presented during that session. Finally, social support for both cessation and adopting home smoking bans was measured using an abbreviated version of the Partner Interaction Questionnaire [61], consisting of six items designed to assess both positive and negative support behaviors [62].

